### **3.5      *Participant Timeline***

The CCKO Evaluation study timeline spans two years from 2016 to 2018, and will be nested in the CCKO Implementation Strategy running until 2020. The specifics of the timeline and milestones for this evaluation project are found in **Figure 5**.

**Figure 5 – Study Timeline**

|                                                      | Allocation and Enrolment       | Post-Allocation |                        |                                                                                      |                                                                                       | Closeout               |
|------------------------------------------------------|--------------------------------|-----------------|------------------------|--------------------------------------------------------------------------------------|---------------------------------------------------------------------------------------|------------------------|
| Time point                                           | -12 mo to 0 (-t 1 ) | 0               | 6 mo (t 1 ) | 12 mo (t 2 )                                                              | 24 mo (t 3 )                                                               | 36mo (t 4 ) |
| Enrolment                                            | X                              |                 |                        |                                                                                      |                                                                                       |                        |
| Eligibility screen                                   | X                              |                 |                        |                                                                                      |                                                                                       |                        |
| Consent                                              | X                              | X               |                        |                                                                                      |                                                                                       |                        |
| Allocation                                           | X                              |                 |                        |                                                                                      |                                                                                       |                        |
| Assessments:                                  |                                |                 |                        |                                                                                      |                                                                                       |                        |
| Baseline data collection (i.e., demographics survey) |                                | X               |                        |                                                                                      |                                                                                       |                        |
| Follow-up data collection                            |                                | X               | X                      | X                                                                                    | X                                                                                     |                        |
| Health care utilization                              |                                |                 |                        | X                                                                                    | X                                                                                     |                        |
| Secondary analysis with ICES data                    |                                |                 |                        | [figure not shown] |                                                                                       |                        |
| Data Analysis and Knowledge Translation       |                                |                 | I                      | I                                                                                    | [figure not shown] |                        |

### 3.6 Sample Size

For the RCT, we conservatively project the total sample size to be 140 (70/arm) based on the following criteria: i) Two-sided test of the null hypothesis at the 5% level; ii) Power of 80%; iii) 10% lost-to-follow-up; projected smallest clinically important difference of 0.5 of the within-patient standard deviation, which is recommended by the developer as a moderate effect size (39).

The required sample size is considered feasible as it is estimated that a pool of about 250 patients are readily identifiable for recruitment at CCKO sites.

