### **3.8 Randomization – Sequence Generation, Allocation Concealment and Implementation**

CCKO randomization will be done using a computer-generated algorithm. Eligible children will receive the intervention in either Time 1 (approximately Jan 2017) or Time 2 (approximately Jan 2018). Randomization will be stratified by region/centre. Blocking will be used to ensure that the two comparison groups are about the same size throughout the trial for each site as well as for the trial as a whole. An allocation ratio of 1:1 with random block sizes between 6 and 8 will be used within each stratum (centre). This will help to ensure that clinicians or investigators will not decipher the block size. After patient consent is obtained, the study investigator or his/her delegate will assign the patient a unique identification (ID) number in sequential order that will be used throughout the study.

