These scores will be used as three co-primary outcomes. The appropriate descriptive statistics will be used to compare groups with respect to baseline and demographic variables. Each outcome variable at Month 12 will be compared between groups using an ordinal regression incorporating center as a random intercept and adjusting for the baseline score. A two-sided test of hypothesis will be applied. The Holm-Bonferroni method will be used to deal with multiple testing (the three outcomes), where the overall target type I error rate is 0.05. The principle of intention-to-treat will be applied to the final analysis.

- iv) Child and Parent (Secondary) Outcomes: The data collection at 0 months and 6 months will be used to perform test-retest reliability, to establish baseline reference measures (0, 6, 12 months for this and other phases of intervention), and to assess for stability of outcome changes (24 months). Secondary child and parent outcomes will be compared at 0, 6 and 12 months using Bonferroni corrections to account for multiple testing. All secondary health system outcomes will be compared between the intervention and control as well.

- v) Process Outcomes: Process data collected through patient interviews will be first analyzed one participant at a time without making distinctions regarding the specific sample criteria articulated above. Following that, distinct issues brought forward for the specific sample criteria will be compared and contrasted to the main sample results. All interview data will be analyzed using a descriptive approach. The overarching themes will be selectively coded using the categories of ‘Active Ingredients’, ‘Fidelity’, ‘Dose’, and ‘Context’. The specific sub-themes under these pre-selected themes will be coded inductively.

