- vi) Health Services Use Among Patients excluded from RCT: A secondary analysis will be performed after completion of the primary trial analysis for children who were excluded from randomization (e.g. those judged to urgently need care coordination), as well as those who cannot complete questionnaires (non-English speaking patients). For such children, we will try to find age- and sex-matched controls in the catchment area of London Health Sciences Centre (where there is no complex care program) with similar patterns of health utilization in the year prior to enrolment and meeting criteria for CMC using an administrative database definition that we have used previously. We will employ a differences-in-differences approach comparing changes in health services utilization and cost, patient- (or caregiver-) reported health-related quality of life, and family functioning, for all children before- and after- intervention, controlling for time trends. Other analyses will also determine which predictor variables distinguish trajectories for at risk groups for future work.
- vii) In addition to a complete case analysis, since it was noted on original analysis that there was substantial missing data, the data were analyzed imputing missing values. Missing primary and secondary outcome data were imputed using multiple imputation by chained equations incorporating baseline variables, group assignment and the corresponding outcomes at baseline and 6 months.

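### The 140-patient sample size gives 80% power for one unadjusted 5% test, but three co-primary outcomes are tested by Holm, so on section 3.6's own inputs per-outcome power is about 65–75%

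*Protocol*

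**What the plan says.** Protocol section 3.6 states: "we conservatively project the total sample size to be 140 (70/arm"). The inputs are "Two-sided test of the null hypothesis at the 5% level; ii) Power of 80%; iii) 10% lost-to-follow-up", and a "projected smallest clinically important difference of 0.5 of the within-patient standard deviation". The section does not mention the number of primary outcomes, an adjusted significance level or a baseline correlation.

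Section 3.8 fixes 1:1 allocation.

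Section 3.12 (Primary Analyses) makes three FECC scores co-primary: coordination among providers, coordination between providers and families, and utility of planning tools. Each is compared between groups at Month 12 by ordinal regression with a random centre intercept and adjustment for the baseline score. On multiplicity it says: "The Holm-Bonferroni method will be used to deal with multiple testing (the three outcomes), where the overall target type I error rate is 0.05".

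**The concern.** The sizing and the planned test are both in the protocol, and they differ. Section 3.6 describes one test at 5%. Under Holm with three outcomes, the smallest p-value must reach 0.05/3 = 0.0167, the next 0.025, and the largest 0.05. An outcome that would pass a single 5% test can therefore fail. A reader who takes the 80% as the chance of detecting a 0.5 SD effect on a given co-primary outcome takes it from a calculation that did not allow for this.

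The unit of the effect is also unclear. The comparison is between groups at Month 12, whereas the 0.5 multiplies a within-patient SD. The power implied by 140 patients depends on what that term means.

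**Working it through.** **Inputs from the protocol.** Two-sided alpha 0.05, power 80%, effect 0.5 SD, 10% loss, 70 per arm (section 3.6); 1:1 allocation (section 3.8); three co-primary outcomes, Holm at overall 0.05, baseline-adjusted comparison at Month 12 (section 3.12).

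**Assumptions, not in the protocol.** Correlation between the three outcomes from 0 to 0.7. Baseline to Month 12 correlation r of 0.3, 0.5 or 0.7. Normal or t approximations stand in for the ordinal regression.

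**1. Reproduce 140.** n per arm = 2(1.960 + 0.842)² / 0.5² = 62.8, so 63. Then 63 / 0.9 = 70 per arm, 140 in total. The match is exact for one unadjusted 5% test with 0.5 taken as a standardised between-group difference, so no multiplicity allowance is hidden in it.

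**2. Power at each Holm threshold** (63 evaluable per arm, 0.5 SD, no baseline adjustment):

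| Alpha | Normal approximation | t-test |
|---|---|---|
| 0.05 | 80.1% | 79.5% |
| 0.025 | 71.4% | 70.4% |
| 0.0167 | 66.0% | 64.8% |

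The difference detectable with 80% power at 0.0167 is (2.394 + 0.842) × √(2/63) = 0.58 SD. The t-test also gives 0.58.

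**3. Power under the full Holm procedure.** Three correlated z-statistics were simulated, each effective outcome having mean 0.5/√(2/63) = 2.81 (400,000 draws per scenario, outcome correlation 0 to 0.7):

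| Outcomes with a true 0.5 SD effect | Power for a given effective outcome |
|---|---|
| One | 66% |
| Two | 69–70% |
| Three | 73–75% |

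If all three improve, power to reject all three is 50% at correlation 0, rising to 64% at 0.7. Power to reject at least one is 96% at correlation 0, falling to 83% at 0.7.

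**4. Effect of the planned baseline adjustment.** If 0.5 is a fraction of the between-patient SD, adjustment raises the effective difference to 0.5/√(1 − r²):

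| r | Effective difference | Per-outcome Holm power, one effective to all three |
|---|---|---|
| 0.3 | 0.524 | about 71–80% |
| 0.5 | 0.577 | about 80–88% |

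**5. The two readings of within-patient SD**, both with baseline adjustment and equal variances at the two times.

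- Repeat-measure SD, total SD × √(1 − r): the effective difference is 0.5√(1 − r)/√(1 − r²) = 0.5/√(1 + r), below 0.5 for any r > 0.
- SD of within-patient change, total SD × √(2(1 − r)): the effective difference is 0.5√(2/(1 + r)), above 0.5 for any r < 1.

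| r | Repeat-measure SD: difference, t-test power at 0.0167 | SD of change: difference, t-test power at 0.0167 |
|---|---|---|
| 0.3 | 0.44, 52% | 0.62, 85% |
| 0.5 | 0.41, 45% | 0.58, 79% |
| 0.7 | 0.38, 39% | 0.54, 73% |

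Against the 65% in step 2, one reading lowers first-step power and the other raises it.

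**The case against.** The strongest reply is that the 65–75% is not the power of the planned analysis either. Section 3.12 adjusts for baseline and section 3.6 does not. With a between-patient SD and r near 0.5, per-outcome power under Holm is back at 80% or more. This stands. A reader might infer that the trial is underpowered as analysed, and the protocol does not support that: the outcome depends on an r that it does not give. What the reply cannot do is rescue the stated derivation, which uses no r. At r = 0.3 the shortfall is largely still there unless all three outcomes improve.

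Secondly, Holm allows a claim on each outcome separately, and nothing in section 3.12 requires all three to succeed. If success means at least one, and all three improve, 140 patients give 83–96% before any adjustment. This also stands. Section 3.6 does not say that this is what its 80% means, and a single-test formula does not compute it.

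Thirdly, a reader might infer that the within-patient SD necessarily makes power worse. It does so under one meaning and improves it under the other. Only the need for a definition is established.

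Fourthly, a reader might take the remark in section 3.12 (Additional Analyses, vii), "since it was noted on original analysis that there was substantial missing data", as contradicting the 10% loss assumption. It does not. The remark is retrospective and gives no rate, and missing outcome data is not the same as loss to follow-up. A planning assumption that may have proved optimistic is not an internal contradiction.

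**Conclusion.** The point holds as a mismatch between the sample-size statement and the primary test. On section 3.6's own inputs (63 evaluable per arm, 0.5 SD, no baseline adjustment), per-outcome power is about 65% at the first Holm step and 66–75% under the full procedure, not 80%. The chance of missing a true 0.5 SD effect on a given outcome is thus about 25–35% rather than 20%. The upper end is the first-step threshold alone; with all three outcomes effective it is nearer one in four.

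The figures rest on normal or t approximations. A rank-type efficiency of 0.955 would lower the first-step figure to about 64%, and the planning-tools score, which runs only from 0 to 2, could lose more. The ranges for any or all outcomes rest on an assumed outcome correlation, and the recovery through baseline adjustment on an assumed r.

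The Holm procedure and its type I error control are not in question.

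**What to change.** Leave the sample size at 140 and revise section 3.6 to:

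- state that 140 gives 80% power only for a single two-sided 5% test of 0.5 SD, without allowance for three outcomes;
- give per-outcome power under Holm: 65–75% unadjusted, or the figure for an explicitly assumed and justified baseline correlation;
- give 0.58 SD as the difference detectable with 80% power at 0.0167, on the unadjusted inputs;
- say whether the stated power refers to each, any or all of the co-primary outcomes;
- define the SD that the 0.5 multiplies, in terms that fit a between-group comparison at Month 12.

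Keep the 10% as the planning assumption that it was. Putting the observed evaluable number into section 3.6 would turn an a priori calculation into post hoc power. A null result on any co-primary outcome should be interpreted from its effect estimate and confidence interval.

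The cost is wording in one section, and the stated power becomes less favourable. No patients, tests or significance levels change.

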### 3.7 Recruitment

At the Complex Care Clinic at each site, staff that have legitimate access to their health and contact information will identify and provide a study information letter to eligible patients using the CMC definition in **Figure 2**, who will further be contacted by the research assistant. An approximate 50% recruitment rate from a pool of N=400 (200/year) is conservatively estimated based on previous recruitment and current waitlists. Families who are inpatient or who are attending a clinic visit will be approached in person for consent. Families may also be sent an information package consisting of consent

and assent forms to participate. The research assistant will follow up if a response is not received, and only families that agree to participate would be contacted to set up a phone or in-person interview (based on the method most convenient for participants). Given the geographical distance, it is not feasible to conduct all of the recruitment in person. Every effort will be made to conduct recruitment in person at the Complex Care Clinic, however some recruitment will need to take place over the phone. In order to document consent instances over the telephone, there is a telephone consent form. The questionnaires would take place at baseline, 6 months, 12 months, and 24 months. Upon completion of each set of questionnaires families will be provided with a \$20 gift card to either Shoppers Drug Mart or Wal-Mart as a token of our appreciation for their time. Recruitment for the qualitative interviews would take place toward the end of the study, and a subsample of 25 families would be approached to answer questions about their overall experience with the Complex Care intervention.

### **3.8 Randomization – Sequence Generation, Allocation Concealment and Implementation**

CCKO randomization will be done using a computer-generated algorithm. Eligible children will receive the intervention in either Time 1 (approximately Jan 2017) or Time 2 (approximately Jan 2018). Randomization will be stratified by region/centre. Blocking will be used to ensure that the two comparison groups are about the same size throughout the trial for each site as well as for the trial as a whole. An allocation ratio of 1:1 with random block sizes between 6 and 8 will be used within each stratum (centre). This will help to ensure that clinicians or investigators will not decipher the block size. After patient consent is obtained, the study investigator or his/her delegate will assign the patient a unique identification (ID) number in sequential order that will be used throughout the study.

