## **2.3 Trial Design**

CCKO will utilize a wait-list variation of a randomized controlled trial design (**Figure 1**). The wait-list approach involves rolling out an intervention over time, whereby all participants are randomized into two groups (A and B) to receive the intervention at different time points determined at random (22,23). Group A would receive the intervention immediately (when resources become available; at time 0). Group B would be on the wait-list and receive the intervention after 12 months. This study design uses the time period before the intervention as the control period/baseline, to be compared in parallel to those receiving the intervention (22). Baseline measurements would be collected at month 0, and Groups A and B would be compared at months 6 and 12.

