**Figure 1 – Trial Design**

[figure not shown]

The wait-list design is used in scenarios where it is considered unethical to withhold an intervention or treatment with proven benefits, or if there are logistical or financial constraints that prevent the intervention from being administered at one time point (22,23). This design generates evidence of an intervention program's cost-effectiveness by leveraging real-world operational need for staggered rollout of CCKO to all eligible children for logistical reasons (e.g. high workload for key workers in the first few weeks to months after meeting families in order to create care plans and foster relationships). All CCKO sites intend to deliver care coordination to all eligible children. However given human resource limitations, CCKO program implementation will require the creation of a waitlist in order to be able to include all the patients. With the exception of patients for whom care coordination is urgently required (see exclusion criteria a)-c) in 3.2), all patients referred to CCKO will randomly assigned to either receive the intervention immediately (at the soonest available clinic appointment) or after the waitlist period (1 year). From a research perspective, this approach minimizes the risk of selection bias by retaining the design element of randomization.

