### 3.3 Interventions

Patients will be randomized to receive either *usual care* for 1 year prior to their first clinic appointment (wait list group) or enrolled to be seen as soon as possible in a *complex care clinic* as part of the CCKO initiative. All eligible patients will be randomly assigned to wait list or the clinic prior to being approached for consent to participate in the evaluation of CCKO. The CCKO intervention involves intensive care coordination, defined as: “deliberate organization of patient care activities between two or more participants (including the patient) involved in a patient's care to facilitate the appropriate delivery of health care services. Organizing care involves the marshaling of personnel and other resources needed to carry out all required patient care activities and is often managed by the exchange of information among participants responsible for different aspects of care” (24). Within CCKO, intensive care coordination will specifically include: 1) the tailored, family/health care provider co-creation and regular updating of care coordination plans for each child which will be 2) facilitated and accounted for by key

workers partnering with families. The key worker would have a nursing or nurse practitioner background and will support providers in enacting the coordinated care plan between acute care, primary care, rehabilitation, home and community care. The key worker would be available to provide advice from Monday to Friday, 9 AM – 5 PM, and will also develop plans of care for emergencies after hours as part of care plan development. Resources to maintain intervention fidelity among key workers will be created and checked with oversight by PCMCH and the workers will connect annually in a meeting that will be co-attended by family representatives.

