**Figure 3 – The CMC Family-Engagement Evaluation Framework**

[figure not shown]

Measures representing these outcomes are selected based on their content applicability to the outcomes, proven psychometric performance (reliability and validity) among children and families with chronic health conditions, and the option for child report wherever possible. The family-Engagement Evaluation

includes general and specific outcomes within the domains of service delivery (primary and secondary outcomes); child outcomes (secondary) and parent outcomes (secondary). Feeding and swallowing performance, as well as satisfaction with medical devices and assistive technology, were identified as priorities for the evaluation by patients and clinicians, however these PROMs could not be found in the literature. As part of the Family-Engagement Evaluation, a team of complex care healthcare providers and measurement specialists will be working on developing appropriate measures for these core outcomes. However for the purpose of this study, only outcomes for which there are validated tools will be measured.

An overview of the included outcomes and their measures are presented in **Figure 4**. Selected outcomes will be assessed at enrolment (t=0), 6 months, 12 months, and 24 months post-randomization so that all subjects will be asked to provide two full years of data. A demographics survey will also be administered during enrolment to capture descriptive, background information of the two groups at baseline. Demographics information includes: sex, age, ethnic background, marital status, education level, and employment status. Qualitative interviews will be conducted at the end of the intervention with a subsample (n = 25) of families in order to capture their overall experience with the intervention, areas of improvement, barriers and/or challenges associated with the intervention, as well as perceived benefits.

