- iii) Sensitivity analysis #1: a) In order to address potential bias resulting from delays in initiation of complex care coordination after randomization, the primary analysis will be repeated using the initial complex care clinic visit date as the start of the intervention until 12 months from that date. b) To further explore this issue, an additional analysis will be performed through observation of the second year of outcome data post-randomization, using data from ICES. The comparison of Year 1 and Year 2 data will explore differences that may exist (in terms of group differences) and is expected to signal the importance of sensitivity analysis #1.
- iv) Sensitivity analysis #2: To account for health systems changes due to COVID-19 restrictions, which impacted most health service delivery across the country beginning March 13, 2020, an additional cost-effectiveness analysis will be conducted. For this analysis all health

service data collection will be truncated as of March 13, 2020 and the ICER will be calculated including health services use up to that date.

- v) Sensitivity analysis #3: Since health care utilization and costing data are being presented as per patient per year, in order to account for the small number of anticipated patients who may die or lose health insurance (OHIP) eligibility during the study, we will rerun the analyses excluding these patients. If this substantially changes study findings, data will be presented as per patient per month.

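### Section 3.8 starts CCKO at two approximate calendar dates, while 2.3 and 3.3 start it on each child's own clock; the two rules agree only if all children share a time zero near January 2017

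*Protocol*

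**What the plan says.** The protocol describes the start of CCKO in two ways.

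- **Calendar dates.** Section 3.8: "Eligible children will receive the intervention in either Time 1 (approximately Jan 2017) or Time 2 (approximately Jan 2018").
- **Each child's own clock.** Section 2.3 on Group A: "Group A would receive the intervention immediately (when resources become available; at time 0"). On Group B: "Group B would be on the wait-list and receive the intervention after 12 months". The text under Figure 1 in 2.3 has referred patients "receive the intervention immediately (at the soonest available clinic appointment) or after the waitlist period (1 year"). Section 3.3 gives usual care "for 1 year prior to their first clinic appointment (wait list group").

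Assessments follow the child's clock. Section 3.4 places them at enrolment, 6 months, "12 months, and 24 months post-randomization so that all subjects will be asked to provide two full years of data". Section 3.12 sets the primary comparison at Month 12 and starts the one-year economic horizon at randomisation.

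Two places bear on how long enrolment lasts. Section 3.7: "An approximate 50% recruitment rate from a pool of N=400 (200/year) is conservatively estimated". Sensitivity analysis #2 in 3.12 provides that health "service data collection will be truncated as of March 13, 2020".

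**The concern.** The primary analysis compares CCKO with no CCKO at Month 12, so it needs wait-list children to be untreated when they are assessed. A wait that ends on a fixed date meets that need only for children randomised at or before a point twelve months earlier. With rolling entry, a child randomised to the wait list in July 2017 would start in January 2018 under 3.8, six months before that child's Month 12 assessment. An FECC item in the first co-primary score asks about the last six months (3.12), so the whole recall period would be treated time. The between-arm difference would shrink toward zero. From the protocol alone, a reader cannot tell when a wait-list child may start CCKO relative to the primary assessment.

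**Working it through.** **Sample size reproduced.** Section 3.6 gives a difference of 0.5 SD, two-sided 5%, 80% power and 10% loss.
n per arm = 2 × (1.960 + 0.842)² / 0.5² = 62.8, so 63. Then 63 / 0.90 = 70 per arm, 140 in total. This matches the protocol.

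**Does enrolment fit one wave near January 2017?**
- Section 3.7: 400 / 200 per year = 2 years of referrals. At 50% uptake this is about 100 children per year, so 140 children take 140 / 100 × 12 = 16.8 months.
- Section 3.6 cites about 250 readily identifiable patients. At the 50% rate of 3.7 that gives 125, fewer than 140.
- Section 3.12: truncation at 13 March 2020 changes a 12-month horizon only for children randomised after 13 March 2019. Applied to the 24-month extension, it matters only for those randomised after 13 March 2018. Both dates are later than January 2018. A child randomised in January 2017 completes 24 months in January 2019 and is never affected.

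**Exposure at Month 12 if 3.8 governed the wait list.** Let m be months from January 2017 to randomisation.
- m from 0 to 12, Group A assumed to start at once: Group A has 12 months of CCKO, Group B has m, and the contrast is 12 − m.
- m of 12 or more: Group B has no untreated wait and the contrast is 0.
- m from −12 to 0, Group A starting January 2017: Group A has 12 − |m| months and Group B none. The contrast is shortened, not lost.

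**Illustrative power.** Assume the effect is proportional to the exposure contrast: d = 0.5 × contrast / 12, and power = Φ(d × √(63/2) − 1.96), for one test at 5%.

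| All children randomised at m | Contrast (months) | d | Power |
|---|---|---|---|
| 0 | 12 | 0.500 | 80% |
| 3 | 9 | 0.375 | 56% |
| 6 | 6 | 0.250 | 29% |
| 9 | 3 | 0.125 | 10% |

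For uniform accrual over T months (T ≥ 12) from January 2017, the mean contrast fraction is 6/T and the share with no contrast is (T − 12)/T. If accrual starts six months earlier, the pre-2017 part contributes (72 − 18)/12 = 4.5. The part after January 2017 contributes (129.6 − 58.32)/12 = 5.94 if it lasts 10.8 months, and 6 if it lasts 18 months.

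| Assumed accrual | Mean contrast fraction | No contrast | d | Power |
|---|---|---|---|---|
| 12 months from Jan 2017 | 0.50 | 0% | 0.250 | 29% |
| 16.8 months from Jan 2017 | 0.357 | 29% | 0.179 | 17% |
| 24 months from Jan 2017 | 0.25 | 50% | 0.125 | 10% |
| 16.8 months from Jul 2016 | 10.44/16.8 = 0.621 | 0% | 0.311 | 41% |
| 24 months from Jul 2016 | 10.5/24 = 0.438 | 25% | 0.219 | 23% |

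Scaling by the six-month recall period instead, uniform 2017 entry gives Group B (18 + 36)/12 = 4.5 of 6 months exposed (75%). If only half the cohort enters in 2017 and the rest is undiluted, this is 37.5%, so d = 0.3125 and power is about 42%.

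**Per-child rule.** Group B has 0 months of CCKO at Month 12 whatever the entry date. The contrast is 12 months and power is 80%.

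**The case against.** The strongest reply is that 3.8 was never the operating rule. Its dates are marked approximate. Sections 2.3 and 3.3, the post-randomisation assessments and the economic horizon all follow the child's clock. A child randomised in July 2017 cannot start in January 2017, so 3.8 read literally cannot govern later entrants in the intervention arm. The dilution arises only when Group A follows its own clock and Group B the calendar. The evidence of later randomisation itself suggests that the dates were planning dates for a first wave. This stands as a limit on the consequence: the harm is conditional. It does not remove the contradiction, because the sentence sits in the randomisation section, and a word such as approximately does not cover a gap of a year or more.

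A second reply is that enrolment before a common time 0 would reconcile everything. Section 3.5 describes a study running from 2016 to 2018, and Figure 5 has an allocation column from minus 12 months to 0. That reading is coherent and loses nothing, but 3.7 and the March 2020 truncation do not fit it.

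A reader might infer from Figure 5 that some children reach Month 12 before either arm has started. The documents do not support this. Figure 5 puts baseline at 0 and follow-up at 6, 12 and 24 months, and 2.3 starts Group A at time 0. The problem appears only if the study-level enrolment window is combined, child by child, with the post-randomisation timing in 3.4. What remains is that the link between the two clocks is unstated.

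Sensitivity analysis #1 deals with delayed starts by counting from the first clinic visit, so intervention-arm start dates are already needed. It does not address wait-list children who start before their Month 12 assessment.

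**Conclusion.** The inconsistency is real and of moderate severity. Section 3.8 cannot be squared with the per-child wait in 2.3 and 3.3 once enrolment is spread over time, and the protocol's own figures indicate that it is.

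The consequence is conditional and graded. If 3.8 governed, wait-list children randomised during 2017 would be partly exposed at Month 12, and those randomised from about January 2018 would have no untreated wait. Children randomised in the year before January 2017 would keep a treated-versus-untreated comparison with shorter Group A exposure. Under the per-child rule there is no loss.

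A reader might conclude that the trial lost its primary contrast, or that its power fell to one particular value. Neither follows. The figures of roughly 10% to 42% rest on assumed accrual patterns, a proportional effect and a mixed reading of the start rules, none of which the protocol states. They show only that the ambiguity could matter. The sample size of 140 stands.

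**What to change.** Reconcile 3.8 with 2.3, 3.3 and 3.4 so that one start rule applies to each arm; which rule is for the investigators to decide. Name one time zero for all assessments, use it throughout, and say how the allocation column of Figure 5 (minus 12 months to 0) relates to it. State that a wait-list child's Month 12 primary assessment is completed before that child's CCKO start. Record the CCKO start date for every child in both arms, so that any early exposure on the wait list can be counted and reported. The cost is protocol wording and one date field, which sensitivity analysis #1 already needs for the intervention arm. No extra patients or visits are required.
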